### Muscle mass and quality assessment

#### MT and echo intensity (MT_echo_) by ultrasonography

MT and MT_echo_ will be measured by ultrasound images (Mysono U6 EX; Samsung Medison, Gangwon-do, South Korea). For body fluid homogenization, 15 min of rest in the supine position will be allowed, with the lower limbs neutrally positioned and sustained by a Velcro strip. A 7.5 MHz linear-array probe (LN5-12; Samsung Medison, Gangwon-do, South Korea), revested by surface gel, to promote acoustic coupling without dermic compression, will be placed longitudinally to the muscle fibers. The anatomic reference between two MT points of each muscle will be defined by the distal motor point sites used for the electrical stimulation. Additionally, for the VL, the anatomical reference will be the middle portion between the great trochanter and the lateral epicondyle [68]. For RF, the reference will be set at 50% and at two-thirds of the distance from the anterior superior iliac spine and the superior patella border [51, 69]. Anatomical references for AT will be defined in one-fourth of the distance between the inferior portion of the patella and the lateral malleolus and one-third of the distance between the border of the fibula and the medial malleolus [70]. Sequential images will be acquired with 6 cm of depth and, after digitalization, analyzed using the ImageJ software (National Institute of Health, USA). MT (cm) will be characterized as the perpendicular measurement between the superficial and deep aponeurosis [71]. MT_echo_ (A.U.) will be evaluated using greyscale grading, obtained by the histogram function of the software (0 = black and 256 = white) [72]. Three consecutive images of the same anatomic point will be analyzed, and the mean will be adopted as the final value for MT and MT_echo_ [73]. MT_echo_ will be normalized by MT (i.e., MT_echo_/MT, cm) to explain the effects of alterations on muscle size [57].

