#### Measurement of secondary outcomes

##### Neuromuscular adaptations of muscle mass and strength

Muscle mass and quality adaptations will be assessed daily prior to the first training session (~ 12 h from the last session) and 12 h after the last training session (T2) (until 12 h prior to the coma awakening), to the predicted death or ICU discharge. The muscle mass of the VL, *rectus femoris* (RF), and anterior tibial (AT) will be measured by MT and muscle quality, by echo intensity, both analyses obtained by ultrasound images. If the patient awakes from a coma and has the appropriate cognition to collaborate in active assessments, the global muscle strength will be evaluated by the Medical Research Council (MRC) score after 12 h of T2, in the ICU and at hospital discharge. Adequate cognition will be assessed by the absence of delirium after completing the Confusion Assessment Method for Intensive Care Units (CAM-ICU) score [52].

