### Quality of life assessment

#### Quality of life using the SF-36 questionnaire

Quality of life will be assessed using the SF-36 questionnaire, an instrument of good acceptance, reliability, and validity for ICU patients validated in Brazil and easily administered by telephone [45, 46, 53, 54]. It comprises 8 domains: physical function, role-physical, bodily pain, general health, vitality, social functioning, role-emotional, and mental health. Scores range from 0 to 100, where 0 corresponds to the worst general health status, and 100 corresponds to the best health condition [86–88]. The categorization and description of the methods and analyses are shown in Table 2.

**Table 2 Tab2:** Categorization and description of the methods and analyses of the study variables

Evaluation category	Organic responses	Method of evaluation	Variables in analyses
Safety and applicability	Acute cardiovascular	Pulse wave analysis (PWA)	MAP, SBPc, SBPp, DBPc, and DBPp (mmHg)
Safety and applicability	Acute cardiovascular	Analyses of the vital signs	HR (bpm) and SpO_2_ (%)
Muscle systems	Muscle mass adaptation	Ultrasound image	Muscle thickness (cm)
Muscle systems	Muscle quality adaptation	Ultrasound image	Echo intensity (A. U. from 0 to 256)
Neuromuscular systems	Global muscle strength adaptations	Medical Research Council (MRC) Score	Number scoring (0 to 60)
Physical function	Adaptations in physical function in ICU	Physical Function in the Intensive Care Test Scored (PFIT)	Number scoring (0 to 12)
Physical function	Adaptations in physical functional performance after hospital discharge	Performance in the basic activities of daily living by the Barthel Index (BI) by telephone interview	Number scoring (0 to 100)
Clinical outcomes	Adaptations in quality of life	Medical Outcome Study 36 – Item Short Form Health Survey (SF-36) questionnaire	Number scoring (0 to 100)

*SBPc* central systolic blood pressure, *SBPp* peripheral systolic blood pressure, *DBPc* central diastolic blood pressure, *DBPp* peripheral diastolic blood pressure, HR heart rate, *MAP* mean arterial pressure, *SpO*_*2*_ peripheral oxygen saturation, *ICU* intensive care unit

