Concerning the scope of the investigation, in addition to the daily assessment of muscle mass, we also proposed a broad assessment of the strength, physical function, and quality of life of the ICU coma surviving patients. Thus, we suggest not only assessing the isolated muscular system in the ICU, but also monitoring the functional integration of the systems through functional analysis and the outcome of quality of life.

For muscle mass, the option of measuring the MT by ultrasound images was based on the scientific validation of this method, which is quicker and simpler for bedside conditions than the cross-sectional area assessment [91]. Additionally, MT presents lower measurement errors such as the coefficient of variation and the typical error, when compared to the muscle cross-section area. The elevated coefficient of variation and typical errors demonstrate high variability between two consecutive measurements, which precludes the detection of daily changes in muscle mass in comatose patients. As a consequence, non-detection of slight changes could impair the management of muscle atrophy prevention, and therefore, the clinical evolution of the patients [92].

In addition to the assessment of muscle mass, muscle quality was evaluated using the MT_echo_ analysis. This method consists of classifying the ultrasound images through greyscale grading, which varies from 0 to 256, where 0 means low gray coloration and 256, intensive gray coloration and characterizes the presence of edema, fat or healthy muscle tissue [72]. Thus, in addition to muscle mass, ultrasound images can assess muscle quality, which involves not only muscle fibers, but also the presence of inflammatory liquid and/or intramuscular fibrosis acquired from low mobility changes, intensive therapy strategies, and exercise-related muscle damage. Additionally, muscle quality assessment allows normalization of MT to the respective echo intensity. This strategy overlooks changes in edema or fibrosis in the MT results, suggesting that the promoted changes are mainly due to the real effect of resistance training on muscle mass [93].

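### Dividing echo intensity by muscle thickness builds muscle loss into the quality index instead of removing it, and the article does not say consistently which variable is analysed

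*Protocol article*

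**What the plan says.** Four places in the protocol article bear on this.

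- **Neuromuscular adaptations of muscle mass and strength** (secondary outcomes): muscle mass "will be measured by MT and muscle quality, by echo intensity, both analyses obtained by ultrasound images". Thickness is the mass outcome and echo intensity is the quality outcome.
- **MT and echo intensity by ultrasonography**: thickness, in cm, "will be characterized as the perpendicular measurement between the superficial and deep aponeurosis". Echo intensity, in A.U., "will be evaluated using greyscale grading, obtained by the histogram function of the software (0 = black and 256 = white"). The mean of three images is the final value of each. The section then adds that echo intensity "will be normalized by MT", as the ratio MT_echo/MT with the unit printed as cm, and gives a purpose that refers to muscle size.
- **Table 2**, which lists the variables in the analyses (placed under the SF-36 heading): muscle quality appears as "Echo intensity (A. U. from 0 to 256"), with no ratio.
- **Discussion**: "muscle quality assessment allows normalization of MT to the respective echo intensity". The purpose given there is to keep oedema or fibrosis from influencing the thickness result.

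The Statistical analysis section applies a mixed model to each dependent variable, without saying which form of the quality variable is meant. The Background hypothesises that BFRp will lessen atrophy and that BFRpE will prevent it.

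**The concern.** The stated purpose of the division is "to explain the effects of alterations on muscle size". The wording is loose, but the natural reading is an adjustment for muscle size. Dividing by thickness achieves that only if echo intensity varies in proportion to thickness, and the article does not claim that it does. Otherwise the division puts the change in thickness into the quality variable with its sign reversed.

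This matters because thickness is itself an outcome, comes from the same images, and is hypothesised to fall by different amounts in the three arms. If that hypothesis is right, the ratio will shift between arms even where the grey level of the muscle is the same. A reader could then count one effect, less atrophy, as two: less atrophy and better muscle quality. The ratio can also fail in the other direction. If oedema brightened the image and thickened the muscle by similar proportions, the ratio would hardly move although echo intensity had changed.

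The article also leaves open whether the analysed variable is raw echo intensity, echo divided by thickness, or both. These can give different answers about quality.

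**Working it through.** The article states no figure for this ratio, so there is nothing to reproduce. The check is algebra on its definition.

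**Inputs from the article.** R = E/M, where E is echo intensity (A.U., 0 to 256) and M is thickness (cm). The unit of R is therefore A.U./cm; the ultrasonography section prints cm.

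**Inputs assumed.** The article gives no expected thickness loss, SDs or correlation. I used thickness losses of 5 to 20%, SDs of log change of 0.05 to 0.10 for M and 0.03 to 0.15 for E, and correlations between the two changes of −0.5 to 0.5.

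**Step 1: how thickness enters.** Change in log R = change in log E − change in log M. The change in thickness enters at full weight, with reversed sign.

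**Step 2: echo unchanged, fractional thickness loss a.** Change in R = 1/(1 − a) − 1.

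| Thickness loss | Calculation | Change in R | Change in raw echo |
|---|---|---|---|
| 5% | 1/0.95 − 1 | +5.3% | 0% |
| 10% | 1/0.90 − 1 | +11.1% | 0% |
| 15% | 1/0.85 − 1 | +17.6% | 0% |
| 20% | 1/0.80 − 1 | +25.0% | 0% |

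**Step 3: contrast between arms.** One arm loses 15%, another 5%, both assumed, with the same starting thickness and identical echo intensity. Ratio of R between arms = (1/0.85)/(1/0.95) = 0.95/0.85 = 1.118. R is 11.8% higher in the arm with more atrophy. Read the other way, 0.85/0.95 = 0.895, so it is 10.5% lower in the arm with less. The contrast in raw echo is zero.

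**Step 4: masking.** If echo and thickness both rise by 10%, R changes by 1.10/1.10 − 1 = 0%, while raw echo shows +10%.

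**Step 5: limits of the effect.** R stays constant if echo falls by the same percentage as thickness, and falls if echo falls by more. The share of variance in the change of log R explained by the change in log M is (ρ·s_E − s_M)² / (s_E² + s_M² − 2ρ·s_E·s_M), where s_E and s_M are the SDs of log change and ρ is their correlation.

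- Uncorrelated changes, s_M = 0.05, s_E = 0.15: 0.0025/0.0250 = 10%.
- Uncorrelated changes, s_M = 0.10, s_E = 0.03: 0.0100/0.0109 = 92%.
- ρ = 0.5, s_M = 0.05, s_E = 0.10: the numerator is (0.05 − 0.05)², giving 0%.
- ρ = −0.5, s_M = 0.10, s_E = 0.03: 0.013225/0.0139 = 95%.

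A simulation over the same grid agreed: 0 to 95% overall, and 10 to 92% with uncorrelated changes. At an assumed mean log change in thickness of −0.12 and no mean change in echo, the ratio rose in 71% to nearly 100% of simulated patients.

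**The case against.** The strongest reply is that the ratio is only a derived index. The outcome section assesses quality by echo intensity, the ultrasonography section keeps the mean of three images as the final echo value before it mentions the ratio, and Table 2 lists raw echo intensity alone. On that reading the sound variable is already in the plan. This stands in part: the quality outcome is not solely the ratio. But the Methods also state that the normalisation will be done and do not say which form the analysis uses.

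A reader might infer more: that the quality index worsens whenever muscle shrinks, that it merely repeats the atrophy result, or that the trial will report a spurious second significant finding. The documents support none of these. The index rises only if echo does not fall by at least the same percentage. It still contains echo intensity, and its overlap with thickness could lie almost anywhere under plausible SDs. The percentages above are not tests, and a pilot of 39 patients in three arms gives no ground for assuming significance.

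The Discussion sentence may also describe a different variable, thickness adjusted for echo, and not a reversed quality ratio. That is a fair reading, but the Methods define no such variable, so the sections still need reconciling.

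Finally, this is one secondary outcome in a pilot whose primary objectives are cardiovascular safety and applicability. Nothing primary depends on it, which limits the weight of the point but does not remove it.

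**Conclusion.** The point holds in a limited form. The formula does not remove the effect of muscle size; it adds the change in thickness with reversed sign. The Step 2 figures follow from the definition once echo is held unchanged. The 11.8% contrast rests in addition on assumed losses of 15% and 5%. An arm difference in atrophy would therefore carry into the ratio and could be taken for a separate effect on quality. How much of the ratio's movement would be thickness and how much echo cannot be settled from the article.

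The inconsistency between sections needs no assumption: the outcome section and Table 2 give raw echo intensity, the ultrasonography section adds echo divided by thickness with a wrong unit, and the Discussion describes thickness normalised to echo. This should be corrected before analysis, because the choice of variable changes what can be concluded about muscle quality.

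**What to change.** 1. State raw echo intensity (A.U., 0 to 256), as already listed in Table 2, as the muscle-quality outcome, analysed with baseline echo intensity taken into account.
2. Drop MT_echo/MT, or label it exploratory. If it is kept, give its unit as A.U./cm, say which direction is read as worse, and state that it is not evidence on quality independent of thickness.
3. Align the ultrasonography section, Table 2 and the Discussion. If the Discussion means thickness adjusted for echo intensity, define that variable in the Methods as a muscle-mass analysis.
4. Treat any model of echo intensity that includes thickness from the same visit as supportive only. That thickness is measured after randomisation and may be affected by treatment, so the adjusted arm contrast is not a plain treatment effect.

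The cost is a change of wording. Both variables are already measured from the same images, so no new data or visits are needed.

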### Muscle strength assessment

#### Global muscle strength by MRC score

Six muscle groups of the upper and lower limbs will be assessed bilaterally through the global strength (shoulder abductors, elbow flexors, wrist extensors, hip flexors, knee extensors, and feet dorsiflexors) by the MRC score [51, 74, 75]. Test familiarization will be performed through passive movements, and the tests will be applied in a fixed order. All muscle groups will be rated from 0 to 5, where 0 means absence of visible/palpable muscle contraction and 5 means movements performed against gravity and resistance [75]. For the fragile and critical population, patients will be positioned in dorsal decubitus with the headboard angled at 45°. Then, arm abduction will be tested against gravity with the elbow in flexion. In case of a successful attempt, the strength will be rated from 4 to 5. Otherwise, patients will be repositioned in dorsal decubitus at 10°. to be rated from 0 to 3. Following that, the elbows, wrists, hips, knees, and ankles will be tested. In case any muscle group cannot be evaluated due to a central/peripheral nervous injury or orthopedic problems, the total sum will be calculated by extrapolating the identical contralateral muscle [20]. The weakness acquired from the ICU will be identified from scores < 48 [76] and classified as severe weakness if < 36 points [75].

### Physical function assessment

#### Physical function by the PFIT scored

The PFIT scored will be applied to measure the physical function of the ICU patients. The score presents four items (assistance with sit to stand, cadence, strength of the shoulder flexors, and strength of the knee flexors), and for each item, the scoring varies from 0 to 3. The maximal score is 12, which indicates functional independence [77]. The PFIT scored will be applied through the translated and validated version for the Brazilian population [78].

#### Physical function by the Barthel Index

The Barthel Index is widely used in Brazil [79, 80] and is applied in severely ill patients [81–83] and administered by telephone [84, 85]. It comprises 10 items weighted differently. Two items (bathing and personal care) can be graded in two alternatives (0 and 5 points), whereas 6 items (feeding, dressing, bowels [fecal and urinary continence], toilet use, stairs), in three alternatives (0, 5, and 10 points), and two items (transfers and mobility) present four alternatives (0, 5, 10, and 15 points). The final score is obtained by summing each item, varying from 0 (complete dependence) to 100 (independence) [44].

### Quality of life assessment

#### Quality of life using the SF-36 questionnaire

Quality of life will be assessed using the SF-36 questionnaire, an instrument of good acceptance, reliability, and validity for ICU patients validated in Brazil and easily administered by telephone [45, 46, 53, 54]. It comprises 8 domains: physical function, role-physical, bodily pain, general health, vitality, social functioning, role-emotional, and mental health. Scores range from 0 to 100, where 0 corresponds to the worst general health status, and 100 corresponds to the best health condition [86–88]. The categorization and description of the methods and analyses are shown in Table 2.

**Table 2 Tab2:** Categorization and description of the methods and analyses of the study variables

Evaluation category	Organic responses	Method of evaluation	Variables in analyses
Safety and applicability	Acute cardiovascular	Pulse wave analysis (PWA)	MAP, SBPc, SBPp, DBPc, and DBPp (mmHg)
Safety and applicability	Acute cardiovascular	Analyses of the vital signs	HR (bpm) and SpO_2_ (%)
Muscle systems	Muscle mass adaptation	Ultrasound image	Muscle thickness (cm)
Muscle systems	Muscle quality adaptation	Ultrasound image	Echo intensity (A. U. from 0 to 256)
Neuromuscular systems	Global muscle strength adaptations	Medical Research Council (MRC) Score	Number scoring (0 to 60)
Physical function	Adaptations in physical function in ICU	Physical Function in the Intensive Care Test Scored (PFIT)	Number scoring (0 to 12)
Physical function	Adaptations in physical functional performance after hospital discharge	Performance in the basic activities of daily living by the Barthel Index (BI) by telephone interview	Number scoring (0 to 100)
Clinical outcomes	Adaptations in quality of life	Medical Outcome Study 36 – Item Short Form Health Survey (SF-36) questionnaire	Number scoring (0 to 100)

*SBPc* central systolic blood pressure, *SBPp* peripheral systolic blood pressure, *DBPc* central diastolic blood pressure, *DBPp* peripheral diastolic blood pressure, HR heart rate, *MAP* mean arterial pressure, *SpO*_*2*_ peripheral oxygen saturation, *ICU* intensive care unit

## Statistical analysis

After data collection, participants will be distributed into subgroups by periods in coma (2, 3–4, 5–6 days), in alertness (1–2, 3–4, 5–6 days), and in ICU permanence (3–4, 5–6, 7–8, 9–10, 11–12 days). The normality of data will be analyzed using the Shapiro-Wilk test. One-way analysis of variance (ANOVA) will be used for intra-group comparisons in T0. A mixed-model analysis will be used for each dependent variable, whereas group and time will be considered as fixed factors and subject as the random factor. In case of significant *F*, the Tukey adjustment will be applied for multiple comparisons. In the event of a non-normal data distribution, a Kruskal-Wallis test will be applied to test for the differences in baseline values and the Friedman test to analyze the repeated measures. The adjusted *p* values will be calculated using the Hommel procedure [48]. Effect sizes between and within groups will be calculated using Cohen’s *d* [89]. The minimal clinically important difference will be assessed with distribution-based methods [90]. The statistical significance will be assessed at *p* < 0.05. All analyses will be performed using R 3.6.2 (The R Project for Statistical Computing, 2019) in R-studio 1.3.443 (RStudio Inc., Boston, MA, USA).

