### Sample size rationale

A total of 30 participants were used for the sample size calculation of the clinical trial [43]. Therefore, a sample of 39 patients will enable 10% sample loss for each experimental group (PM/control, BFRp, and BFRpE). Based on a recruitment average of 24 patients per month, 20% of non-consent and 30% of non-previewed death or immediate discharge, we aimed to recruit 7.2 patients per month. The recruitment in a single ICU will allow the study to be completed in a minimal period of 6 months.

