Regarding the trial design, the inclusion of patients within the first 18 h of coma identification was suggested to promote a higher experimental control. The aim of this was to ensure that there would be enough time to perform the admission procedures and the first training session, before the beginning of the deleterious effects associated with low mobility [15, 16].

Another control that was adopted was the randomization of patients into experimental groups by ranking the characteristics that could impair the between-group comparison. More specifically, a peculiar aspect of intensive care studies is the high variability of the sample characteristics, principally in adult ICUs, where the admission involves non-pediatric patients of both sexes, with all types of clinical severe illness, pre- and post-surgery. Thus, to homogenize the experimental groups, we purposely stratified the participants into quartiles, considering MT and type of disease.

To further enhance trial control, our study also proposed daily assessments involving muscle mass. This strategy enables a detailed and trustworthy monitoring of the training-related responses, which differs from specific evaluations, performed during the pre- and post-training period. In addition, this strategy may be important for the experimental and statistical adequacy of the clinical trial to intensive care, in which daily pre- and post-session assessments allow lower experimental losses. Thus, in the event of unanticipated patient discharge or death, the statistical analysis may include the last assessment data from the previous day.

Despite the positive aspects presented, the study is not without limitations. The inclusion of patients with varied duration of coma (2–6 days of intervention and 2 to 12 days of ICU permanence) may lead to high heterogeneity at both time points. As an alternative, the use of subgroups for the duration of the coma (2–3, 4–5, and 6 days), alertness (1–2, 3–4, and 5–6), and the time of stay in the ICU (3–4, 5–6, 7–8, 9–10, and 11–12) was suggested. Finally, the patients who were not classified in the study groups or in the added subgroups should be included in the clinical trial flowchart, but not in the statistical analysis.

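### The normality check that decides whether the mixed model is kept is run on the raw, repeated data and not on the model's residuals, so it can reject a correct model well above 5% of the time

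*Protocol article*

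**What the plan says.** All of this stands in the Statistical analysis section unless noted.

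- **Object of the check:** "The normality of data will be analyzed using the Shapiro-Wilk test". Residuals are not mentioned anywhere in the article.
- **Planned model:** a mixed model for each dependent variable, in which "group and time will be considered as fixed factors and subject as the random factor".
- **Trigger and consequence at baseline:** "In the event of a non-normal data distribution, a Kruskal-Wallis test will be applied to test for the differences in baseline values".
- **Consequence for outcomes measured more than once per patient:** under the same trigger, the stated replacement for the mixed model is "the Friedman test to analyze the repeated measures".
- **Level:** "The statistical significance will be assessed at *p* < 0.05". No other level is given for Shapiro-Wilk, so 0.05 is assumed for it too.
- **Structure of the data:** under Neuromuscular adaptations of muscle mass and strength, "Muscle mass and quality adaptations will be assessed daily prior to the first training session". The sections on acute cardiovascular responses and pulse wave analysis place readings before, during and after the first session. Both sets of values repeat within a patient.

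The article does not say whether the check pools all values or is made by arm, by day or by arm-by-day cell. It also does not say how many failures trigger the switch.

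**The concern.** Two mismatches meet in this rule. First, the model needs normal residuals and normal patient effects, and a test on raw values examines neither directly. Second, Shapiro-Wilk takes its reference distribution from independent values. When each patient contributes several similar scans, the pooled sample is a set of tight clusters. The test judges it as though it held as many independent values as there are scans, although it carries little more information than one value per patient. It can then reject because a patient's scans resemble each other, which is exactly what the random subject factor is there to handle.

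The cost lies in what follows a rejection. The Friedman test ranks times within patient. It has no group factor and needs complete blocks, while the number of scans varies with length of coma. A false trigger therefore removes the between-arm comparison over time and drops patients who have fewer scans. The abstract says that these data will inform the design and sample size of a later trial, so losing that comparison matters even in a pilot.

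**Working it through.** The article states no error rate for this check, so there is no figure of its own to reproduce. The check is a simulation in which the mixed model is exactly true.

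**Inputs from the article**
- 39 randomised patients in three arms, 13 per arm (Sample size rationale). The same section has "A total of 30 participants were used for the sample size calculation of the clinical trial"; using 30 gives nearly the same rates.
- Daily scans over a predicted coma of 2 to 6 days (Table 1), so 2-6 scans per patient, or 3-7 when the scan after the last session is counted.
- Shapiro-Wilk at 0.05.

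**Assumed:** the ICC, which the article does not give. It was varied over a wide range.

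**Model:** y_ij = mean + b_i + e_ij, with b_i normal with variance ICC and e_ij normal with variance 1 − ICC. Every single value is then exactly normal with variance 1, so any rejection above 5% is false and comes from dependence or from multiple testing.

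**Number of pooled values:** on average 39 × 4 = 156 with 2-6 scans, or 39 × 5 = 195 with 3-7 scans, from only 39 patients.

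**Pooled test, rejection of a correct model (39 patients)**

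| ICC | Pooled test rejects |
|---|---|
| 0.5 | 9-10% |
| 0.7 | 18-22% |
| 0.8 | 26-34% |
| 0.9 | 45-55% |
| 0.95 | 62-71% |

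At ICC 0.3 the pooled rate is close to nominal (3-8%). With only two scans per patient at ICC 0.8 it is 10-12%.

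**Other readings of the rule**
- Any of the three arms failing: about 19-22% at ICC 0.5, 50-60% at 0.8 and 91-96% at 0.95. With independent values it would be 1 − 0.95³ = 14%.
- Any single day failing: about 22-30%, with little dependence on ICC.
- Any arm-by-day cell failing: about 40-56% at every ICC studied. Here the cause is the number of tests. For 3 × 6 = 18 independent cells, 1 − 0.95¹⁸ = 60%; patients' values are correlated across days and late cells are sparse, which lowers it.
- One time point only: about 5%.

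**Cardiovascular variables**, taken as three fixed times with ICC 0.7 to 0.9: pooled 13-30%, any arm-by-time cell about 33%.

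**Check on the right object:** the true errors are rejected in about 5%. Conditional residuals and predicted patient effects are each rejected in 1-7% over runs of 300 trials, centred near 5%. The residuals of a fitted random-intercept model were rejected in 4.4% of 250 trials.

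**The case against.** The strongest reply has four parts.

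1. The word data may be loose shorthand for residuals, and the unit of testing is a detail that an article can leave to a fuller plan. The second half stands, and it is why no single rate can be given. The first half may be true, but the text names the data as the object and ties the switch to their distribution.
2. No ICC is given. The Discussion says that muscle thickness has lower measurement error than cross-sectional area and that ICU patients vary widely. Both point to a high ICC, but neither fixes a value. This stands.
3. If only one time point is tested, the rate is about 5%. This also stands, but nothing in the text limits the check to one time point.
4. The scans are secondary outcomes in a pilot, and the main safety and applicability decisions rest on threshold and count rules that this check does not touch. This limits the stakes.

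A reader might also infer more than the article supports:

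- **That the model will be discarded in a quarter to nearly all cases.** The lower end needs an ICC of about 0.8 or more. The upper end needs an any-arm-fails rule as well. The article states neither.
- **That a real treatment effect makes it worse.** Arms that start alike and diverge by 0.1 SD per day lowered the pooled rate, from 55% to 46% at ICC 0.9 and from 71% to 59% at 0.95.
- **That mixing men and women adds to the false triggers.** The article does describe admission "in adult ICUs, where the admission involves non-pediatric patients of both sexes". But sex is not among the model's stated factors, so a large sex difference would make the patient effects truly non-normal. A rejection would then not be false.
- **That the nominal 0.05 level is broken.** Only the trigger rate was measured. The type I error and power of the whole two-stage procedure were not.

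**Conclusion.** The rule is wrong as written. It uses a test for independent values on repeated raw data to decide whether to keep a model that assumes nothing about pooled raw data. When the model is exactly true, the false-trigger rate exceeds 5% under every reading that pools a patient's repeated values at ICC 0.5 or above, and under every reading that tests several days or cells separately. How far above depends on the ICC and on the testing unit: about 9-10% for a pooled test at ICC 0.5, 62-71% at 0.95, and 40-56% for cell-by-cell testing at any ICC studied. These figures assume 39 patients, 2 to 7 scans each, a 0.05 level for Shapiro-Wilk, and normal patient effects and errors. The consequence is loss of the between-arm comparison over time for the outcomes affected. The defect is specific and cheap to correct, and it does not reach the threshold-based safety decisions.

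**What to change.** - Delete the switch that depends on Shapiro-Wilk of the raw data.
- Fit the mixed model for muscle thickness, echo intensity and the cardiovascular variables. Check its residuals and predicted patient effects with Q-Q and residual plots.
- If these are clearly non-normal, keep the same arm-by-time contrast, using a transformation stated in advance or a patient-level permutation or bootstrap p value.
- For the bounded scores (MRC, PFIT, Barthel, SF-36), use the same arm contrast with the permutation or bootstrap p value from the start, so that these outcomes are not left without a rule once the switch is gone.

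The cost is a change of wording in the analysis section, with no extra data. The small downside is that reading residual plots takes judgement, which is best exercised blind to arm. If residuals were meant all along, replacing the object of the check still leaves the Friedman fallback to be changed, because it cannot compare the arms.
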